## Abstract

**Introduction:**

Despite being a life-preserving medical treatment, the demands of haemodialysis are a significant impost on individuals, posing considerable burdens on their work, vocational activities and involvement with family and community. In our region, patients who have had to relocate considerable distances to a regional city for dialysis, and First Nations people, are less likely to attend all scheduled dialysis sessions. Virtual reality (VR) has been shown to improve engagement with care of people on haemodialysis.

This manuscript describes the protocol for a cross-over randomised controlled trial (RCT) that will explore the impact of an immersive VR experience for patients attending a northern Queensland, Australia, haemodialysis service.

**Methods:**

The design is a crossover RCT, with 8 clusters according to haemodialysis location and schedule. Clusters (5 participants in each) will be randomized by computer program. Participants in the trial will be patients who undergo haemodialysis three times/week at one of two dialysis units. During the 4-week intervention period (12 haemodialysis sessions), participants will be provided a headset with vision representative of the natural environment, and with audio. The 4-week control period will comprise usual activities, such as watching television, reading and sleeping. Outcomes will be measured by participants': attendance at scheduled dialysis sessions; adherence to lifestyle modifications; wellbeing, anxiety and depression; acceptability and usability of VR; and adverse events such as nausea. The feasibility and acceptability of the intervention from clinicians’ perspectives will also be explored.

**Discussion:**

If this VR intervention is feasible, then participants may engage more with haemodialysis regimens and self-care in this very clinical environment.

**Trial registration:**

ACTRN12621000732886.

## Introduction

1

Despite being a life-preserving medical treatment, the demands of haemodialysis place a significant impost on individuals, with substantial burdens on work, vocational activities and involvement with family [1], often leading to poor attendance at clinic appointments and poor adherence to treatment plans [2]. Factors such as geographical accessibility and cultural acceptability of treatment procedures have been associated with irregular clinic attendance among patients on long-term haemodialysis [3,4]. From a previous retrospective chart review [2], it is known that Aboriginal and/or Torres Strait Islander patients were statistically less likely to attend all scheduled dialysis session, as were patients who have had to relocate from rural settings to the regional city for their dialysis. Interventions to optimise engagement with care and avoid emergent dialysis are urgently needed.

The provision of such interventions is particularly important for First Nation peoples. In northern Queensland the prevalence of end-stage kidney disease demonstrates an inequity: approximately 65% of the Townsville Hospital and Health Service renal patients are of Aboriginal and/or Torres Strait Islander descent, whilst this group constitutes only 7.9% of the Health Service's residents [5].

Findings from our systematic review investigating the effects of virtual reality (VR) on the lives of people receiving haemodialysis [6] favour the use of VR to improve engagement with treatment and thus physical health. However, no studies have been undertaken in Australia with individuals undergoing haemodialysis.

### Background

**1.1**

Immersive VR, where a person is exposed to video and sound via a head-mounted display and is isolated from the external world [7], has been shown to be more effective across different domains and settings than traditional two-dimensional (2D) or three-dimensional (3D) video. For example, participants reported greater ‘presence’ when playing a video game in immersive VR format compared to 2D or 3D formats [8], and a greater sense of awe [9,10], and better cognitive function (memory) [11]. Findings from randomised controlled trials (RCTs) of VR in haemodialysis sessions have produced different responses with respect to depression. Non-immersive virtual reality combined with exercise significantly reduced depression in a sample of patients undergoing haemodialysis in Qatar [12] but had no effect in a similar study undertaken in Brazil [13]; different measurement tools were used [6].

It is acknowledged that VR may have the potential to evoke nausea or a sense of motion sickness, as identified by a crossover observational study involving volunteers watching 3D movies [14]. However, a quasi-experimental study undertaken in a haemodialysis setting [15] demonstrated that immersive VR did not worsen a participant's usual symptoms of headaches or nausea. A recent systematic review identified that VR was generally acceptable and safe in a haemodialysis setting, although most studies have used non-immersive VR to promote exercise [6].

Haemodialysis units are clinical, medicalised environments. It is proposed that a VR intervention that is engaging, such as the opportunity to ‘travel through landscapes’, will enable a person to feel more at ease and disengaged from the aspects of the surrounding treatment environment which may arouse anxiety.

The aims of this study are to explore the feasibility of an immersive VR experience for patients undergoing haemodialysis; and to inform a multi-centred RCT on the effects of VR for patients undergoing haemodialysis.

## Methods

2

### Study objectives

2.1

The primary objective is to:-compare participants' adherence to haemodialysis regimens (with respect to attendance at scheduled dialysis sessions) between the intervention and control phase.

The secondary objectives are to:-compare participants' adherence to haemodialysis regimens (with respect to adherence to fluid allowances) between the intervention and control phases;-measure change in ratings of quality of life, engagement with self-care and other psychological measures reported by participants between the intervention and control phases;-measure usage and usability of VR by participants;-assess the acceptability and appropriateness of using VR during haemodialysis from the perspectives of patients; and-assess the acceptability and appropriateness of using VR during haemodialysis from the perspectives of clinical staff.

### Project design

2.2

A crossover RCT will be conducted where participants are their own control. Such a study design requires fewer participants, maximises equivalence between groups and controls for confounding variables [16], compared to traditional parallel RCTs. Consistent with this design, a one-week washout period between the intervention and control phases will be included to minimise any carry over effects [16]. Clusters have been determined by place of dialysis (in-centre or satellite dialysis unit), and scheduled days of dialysis. Each of the 8 clusters will consist of 5 participants (as described later in section 2.9.4).

### Intervention

2.3

An immersive VR experience (choice of simulations of 30–40 min in duration) can be used at any time during each dialysis session. All-in-one Oculus Quest 2 headsets, not requiring an external computer to connect, will be used in this study to provide the best immersive experience and performance possible. Oculus Quest 2 devices are equipped with 64 Gb, two 6 Degree-of-Freedom controllers to support both orientation and positional tracking and can provide high resolution with lower latency to maximise virtual experience and minimise motion sickness [17]. Several VR simulations will be created using localised natural sounds and scenes to have more contextualised immersive experiences. Headsets will be distributed to each participant for the period of the intervention; they will be cleaned as per the Health Service's infection prevention and control practices between participant groups (see safety considerations/Patient safety section). Headsets have been fitted with spacers to accommodate participants wearing their glasses if they wish. The Intervention period will be four weeks' duration.

### Control

2.4

The Control period will be four weeks’ duration and involve usual activities, such as watching television, sleeping and reading.

### Project setting and population

2.5

The project is set in the in-centre dialysis unit at Townsville University Hospital (TUH) and the satellite dialysis unit at North Ward (NW). There are approximately 110 patients undergoing haemodialysis at TUH and 44 patients at NW.

### Project duration/timeline

2.6

This study is anticipated to take two years. If additional equipment is available, it may be possible to complete the crossovers earlier than anticipated.

### Participants

2.7

There are two groups of participants: one group comprises patients undergoing haemodialysis, and another group comprises clinicians caring for patients undergoing haemodialysis. Target users are a small group of patients undergoing haemodialysis who will provide feedback to assist the development of the VR experience video.

#### Group 1: Patients undergoing haemodialysis

2.7.1

Selection criteria are informed by a previous study [18]. Outpatients attending haemodialysis at TUH or NW with the following characteristics will be included: 18 years or older; in treatment with three haemodialysis sessions per week; haemodialysis duration of 3 h or greater; no history of severe migraines; and orientated to time and space. It is expected that some participants will be First Nations people.

#### Group 2: Clinicians

2.7.2

Clinicians (nurses, doctors and health workers) providing care to patients in Participant Group 1 during the VR intervention.

### Sample size calculation

2.8

The sample size of Group 1 (patients) of n = 40 is informed by other feasibility studies included in our recent systematic review [6]. The within-subject crossover design minimises sample variability as all participants act as their own controls [19]. Given that the current study is a feasibility analysis, there is less emphasis on hypothesis testing and more upon the appropriateness of the intervention and applicability of the measures for assessing physical and psychological status in this patient population. Our sample size for this feasibility study is based upon empirical literature reports of similar studies and practical limitations upon recruitment, rather than statistical calculations.

With regards to the clinicians (Group 2), we will invite all clinicians (nurses, medical officers, allied health staff) to complete an anonymous questionnaire. It is anticipated that approximately 50% of clinicians will participate.

### Project outcomes

2.9

The primary outcome is attendance at scheduled dialysis sessions.

The secondary outcomes are:-Adherence to fluid allowances between dialysis sessions;-Health related quality of life;-Engagement with self-care;-Depression and anxiety;-Usage, acceptability and usability of VR; and-Participants' (patients and clinicians) satisfaction with VR.

#### Project outcome measures

2.9.1

Note that the crossover design means that differences being examined are *within* participants [16]. That is, outcomes in the intervention phase are compared to outcomes in the control phase for all participants.

##### Adherence to haemodialysis regimens will be measured by

2.9.1.1

-difference in participants' attendance rates when in the intervention phase compared to the control (non-intervention) phase; and-difference in proportions of participants' adherence to fluid allowances, defined as gaining, on average, no more than 1 kg per day between dialysis sessions in the intervention phase compared to the control phase [2].

##### Health-related quality of life and engagement with self-care

2.9.1.2

This will be assessed by the use of the Australian Assessment of Quality of Life (AQoL) scale (6D) [20]. The scale consists of 20 items across 6 dimensions (independent living, relationships, mental health, coping, pain, and senses), and participants are asked which of five descriptive statements best describes their current experience in terms of the item of interest. The scale was chosen for its brevity, validity and conversational style [20]. Reliability of the tool (Cronbach's α) has been found to range between 0.73 and 0.84 [21]. An example of one of the questions in the scale asks the participant to describe their situation over the past week, with respect to “How much energy do you have to do the things you want to do”.

##### Depression and anxiety

2.9.1.3

This will be assessed by the amended Kessler Psychological Distress Scale – 5 (K-5), which contains 5 statements about an individual's psychological state in the previous 4 weeks [22]. Respondents are asked the extent to which they have felt each of these states (feeling nervous, without hope, restless or jumpy, that everything was an effort, and sad). The K-5 was chosen as it is extensively normed in non-Indigenous populations and it forms part of the Social and Emotional Wellbeing module for Aboriginal and Torres Strait Islander Peoples used by the Australian Institute of Health and Welfare [22]. A recent study assessing the psychometric properties of the K-5 with a sample of Aboriginal and Torres Strait Islanders demonstrated good internal consistency/reliability (α = 0.89), and the scale was deemed to have clinical utility as a screening tool for depression and anxiety with the score of ≥11/25 [23].

##### Participants' satisfaction, usage and usability, and clinicians’ satisfaction measurements

2.9.1.4

Participants' satisfaction with, and immersion in, the VR experience will be measured with the User Engagement Scale – Short Form [24], modified and incorporated into a conversational interview, congruent with a ‘yarning’ method of Indigenous research [25]. Usage and usability of the VR will be measured by the percentage of dialysis occasions that patients use the VR headset, the amount of time within a session the participant used the headset, whether VR is used at the beginning, middle or towards the end of the dialysis sessions. These data are gathered by the headset and uploaded automatically from it. Any difficulties encountered in its use will be likely reported in the delivery of the User Engagement scale above.

Clinicians’ satisfaction will be measured by a questionnaire asking about the acceptability, feasibility, benefits and barriers to using VR in a haemodialysis setting. Due to the novelty of VR in treatment environments, no appropriate standardised assessments for this population group using this technique currently exist. Clinical staff will be asked to complete a survey adapted from Lindner et al. [26]. This assessment asks about clinician familiarity with the medium both in and outside the clinical setting. Respondents are presented with positive and negative aspects of the use of VR (e.g. patient mood improvement versus cost of technology) and asked how concerned they are about each issue. There is an option at the end of the questionnaire for open-ended answers for additional comments.

#### Recruitment and consent of participants

2.9.2

Flyers will be displayed in the TUH in-centre and NW satellite renal units, alerting staff and patients to the study. The study will be explained to the staff of the units during meetings and usual communication channels. Training about the recruitment process will be provided to staff who have never been involved in this process if required.

A Participant Information Sheet and Consent Form will be provided to all potential participants. These documents can be read to potential participants if required. Written consent will be obtained by the patient signing with their name or an X. Participants’ consent will be requested for the collection of demographic characteristics such as: age; ethnicity; living arrangements (whether it is shared accommodation (hostel) or private house; social supports; whether the patient has had to relocate to Townsville for dialysis; distance travelled each day for dialysis); length of time since commenced on dialysis; duration of each dialysis session; intradialytic weight gain and attendance records. Previous research conducted in the renal unit by this team has been successful in terms of participant recruitment [for example, 19].

##### Recruitment of clinician participants

2.9.2.2

All clinical staff in the unit will be invited to participate. They will be informed of the study by way of flyers/ward meetings/ward communication book, and email including a Quick Response (QR) code to the on-line questionnaire. Information will be provided to clinical staff by way of Participant Information Sheet; consent will be provided by checking a box that states, “I agree to complete this questionnaire”, and on-line survey logic will be applied.

#### Withdrawal of participants from the project

2.9.3

There are no consequences for declining to participate in this trial or withdrawing from the study. On any given day during the intervention phase, participants can choose not to wear the headset. Data collected prior to withdrawal will be retained and included in the analysis on an intention-to-treat basis.

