#### Data collection processes

2.9.5

So as not to inconvenience patient participants' routines, the conversational interview about their experiences with VR, and the data related to quality of life and psychological measures will take place during a scheduled dialysis session (in the week following the 4-week intervention/control periods). All data collected directly from the participants will be undertaken in a conversational manner in their familiar surroundings. If the patient prefers, data collection can be undertaken in an office in the renal unit; it is recognised, however, that this would be a less inviting environment and may inhibit conversation. Measures to be used are described earlier in sections 2.9.1.2, 2.9.1.3, and 2.9.1.4. After recruitment and consent, but before their first haemodialysis session associated with the trial, participants will be asked to complete the AQoL-6D and the K-5 at three timepoints: the week prior to first haemodialysis session associated with the trial, the one-week ‘washout period’ between the intervention and control phase (or vice versa) and in the week following involvement in the trial. (Refer to Fig. 1). During the intervention phase, the research assistant/Health Workers/nurses will seek formative feedback about the use of the VR headset. The summative interview (based on the User Engagement scale) will be conducted in the week following completion of the intervention period.

Socio-demographic and clinical related characteristics of participants such as age, gender, relationship status, place of residence, age at initiation of haemodialysis, type of vascular access, cause of renal failure) will be obtained from the participants' medical records by the study's Research Assistant, after patient consent has been obtained. Attendance and intradialytic weight gain will be retrieved from the electronical medical record for each dialysis session.

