#### Data analysis plan

2.9.7

The quantitative data will be entered into an IBM SPSS software (SPSS) database (Version 25, Chicago). Chi-square tests will be used to analyse categorical data. Ordinal data will be analysed via rank tests. Paired t-tests and ANOVA will be used for continuous variables where appropriate. Where assumptions of normality have been violated, non-parametric versions of tests will be used. If participants withdraw, attendance data will be analysed by intention-to-treat. Where appropriate, modelling of outcomes will be undertaken in order to explain variability in results.

Qualitative analysis will include notes taken from informal interviews with patients and will be analysed deductively. Observational and summary notes taken by the investigators, and notes taken by a Stakeholder Group (comprising patient, staff and researcher representatives, who will meet to discuss the progress of the study at least monthly) will also form part of the analysis.

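### The intention-to-treat promise for attendance is not met for participants who withdraw before their second phase

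*Protocol article*

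**What the plan says.** Section 2.9.3 (Withdrawal of participants from the project) states: "Data collected prior to withdrawal will be retained and included in the analysis on an intention-to-treat basis". The same section lets participants leave the headset off on any day, so non-use is not withdrawal. It does not say what happens to records made after a withdrawal.

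Section 2.9.7 (Data analysis plan) adds: "If participants withdraw, attendance data will be analysed by intention-to-treat". Its methods include "Chi-square tests will be used to analyse categorical data", rank tests for ordinal data and "Paired t-tests and ANOVA will be used for continuous variables where appropriate", with non-parametric versions where normality fails. It closes with "Where appropriate, modelling of outcomes will be undertaken in order to explain variability in results". No method is tied by name to attendance.

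Section 2.9 states: "The primary outcome is attendance at scheduled dialysis sessions". Section 2.9.1.1 measures it as the "difference in participants' attendance rates when in the intervention phase compared to the control (non-intervention) phase", and section 2.9.1 says this within-person comparison covers every participant.

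On the data source, section 2.9.5 says: "Attendance and intradialytic weight gain will be retrieved from the electronical medical record for each dialysis session". Section 2.9.2.1 lists attendance records among the items for which consent is sought.

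**The concern.** Keeping a person's data does not ensure that the analysis uses them. The primary contrast is a difference between two phases in the same person. A participant who leaves before the second phase has no such difference if data stop at withdrawal, so the retained data have no route into a paired comparison.

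Two things are at stake. First, the protocol's own rationale is poor attendance and disengagement from treatment, so people who withdraw may well differ in attendance from those who stay. Leaving them out can then bias the contrast. Second, the loss is largely avoidable. Attendance is read from the medical record, and it continues to be recorded for anyone still on the unit's dialysis schedule, whether or not they remain in the trial.

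**Working it through.** **Inputs from the protocol article.** 8 clusters of 5 (section 2.2), which gives 8 × 5 = 40 and matches the stated sample size (section 2.8). 12 sessions per 4-week phase (Abstract, Methods). A one-week washout (section 2.2), which is 3 sessions at three per week. No withdrawal rate, timing or attendance level is given.

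**Step 1: what a paired test does.** A paired t-test run on 40 simulated participants, 5 of them without a second phase, used 35 pairs (34 degrees of freedom). The rank version needs both values too. Repeated-measures ANOVA in its usual complete-case form has the same need.

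**Step 2: who drops out.** Assume withdrawal is spread evenly over the 12 + 3 + 12 = 27 scheduled sessions. Withdrawal in the first 15 leaves no second-phase data:

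- share lost = (12 + 3)/27 = 15/27 = 56%
- share kept, with a rate from a shortened second phase = 12/27 = 44%

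| Assumed withdrawal | Withdrawers of 40 | No second phase | Partial second phase | Pairs left | Strict completers |
|---|---|---|---|---|---|
| 5% | 2 | 1.1 | 0.9 | 38.9 | 38 |
| 10% | 4 | 2.2 | 1.8 | 37.8 | 36 |
| 20% | 8 | 4.4 | 3.6 | 35.6 | 32 |
| 30% | 12 | 6.7 | 5.3 | 33.3 | 28 |

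Timing matters. If every withdrawal came before period 2, all 2 to 12 withdrawers would be lost. If every withdrawal came during period 2, none would be.

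**Step 3: possible bias.** Let m be the number lost. Let G be the mean phase difference in those kept minus that in those lost. Then

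paired estimate − estimate over all 40 = (m/40) × G.

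- G = 5 points: 1.1/40 × 5 = 0.1 point at 5% withdrawal; 6.7/40 × 5 = 0.8 point at 30%.
- G = 25 points: 1.1/40 × 25 = 0.7 point at 5%; 6.7/40 × 25 = 4.2 points at 30%.
- Example at 20%: with a gain of 5 points in those kept and 0 in those lost, the paired estimate is 5.0, against 35.6 × 5/40 = 4.4 over all 40.

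Both values of G are assumptions. If G = 0, nothing is biased and only precision is lost.

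**Step 4: unequal loss by sequence.** Each sequence holds 4 clusters × 5 = 20 people. If 5 are lost, all from one sequence, an unadjusted paired mean carries (20 − 15)/35 = 14% of any period effect. Equal losses carry none.

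**The case against.** The best case on the other side has several parts.

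- **Completers only.** A reader might infer that the primary analysis is confined to completers. The text does not support that. Attendance is a rate, so a person who leaves during period 2 has a rate in both phases and enters a paired test. Anyone who only stops using the headset has not withdrawn. That also weakens the picture of people made unwell by VR being lost, and those allocated to control first who leave in period 1 have not yet had VR.
- **Later data discarded.** A reader might infer that records after withdrawal are thrown away. Section 2.9.3 says earlier data are kept and is silent on later ones. Section 2.9.5 could be read as covering every session. The defect is that the protocol makes no provision for later data; it does not prohibit using them.
- **Conflicting scope.** Section 2.9.3 speaks of data in general and 2.9.7 of attendance. The second restates the rule for one outcome without limiting it, so both can be followed.
- **No test is fixed for attendance.** This is true, and an analysis plan that is not shown may name a model. But the modelling mentioned is optional and is meant to explain variability. Also, whether records are followed after withdrawal must be settled in the protocol and consent form; an analysis plan cannot supply data that nobody had permission to collect.
- **Feasibility.** Section 2.8 puts less weight on hypothesis testing. This bears on severity. It does not make the intention-to-treat statement correct.

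**Conclusion.** The point stands in a limited form. Under the provisions stated, a participant who withdraws in period 1 or the washout cannot contribute to a paired comparison of attendance. The commitment to intention-to-treat and to comparing phases in every participant is therefore not met for that group. The analysis set is those with some data in both phases.

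The size is about 1 to 7 of 40 participants at 5% to 30% withdrawal, assuming even timing. The shift in the estimate runs from 0.1 to 4.2 percentage points over the scenarios above, and is zero if withdrawal is unrelated to the phase difference. These figures rest on assumed rates, timing and gaps, and on attendance being analysed by a paired test without post-withdrawal records.

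This should be fixed because the results are meant to inform a multi-centre trial. Given the feasibility aim, it is not a flaw that invalidates the study.

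**What to change.** 1. In section 2.9.3 and the consent form, separate leaving the intervention or interviews from withdrawing permission to use records. State that attendance and weight-gain records for all 12 + 12 = 24 scheduled sessions will still be retrieved in the first case, and will stop only in the second.
2. In section 2.9.7, state that attendance is analysed for all randomised participants on those data, whether or not they stayed with the intervention.
3. As a secondary step, for those who still have one phase only, use a session-level mixed model for attendance with treatment, period and cluster. Say that it is valid only if data are missing at random. One-phase participants bring between-person information but no within-person contrast, so the model does not replace step 1: if withdrawal depends on unobserved attendance, it will not in general recover the all-participant effect.

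The cost is a line in the consent form, an ethics amendment and revised analysis wording. Record extraction is already planned.
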